### Inclusion criteria

a) Primarily motor symptoms with unilateral upper limb paresis (controlled via standard neurological examination).b) Residual movement ability of the paretic upper limb, controlled by Medical Research Council (MRC) index (> 2 and < 4), active use of the hemiplegic limb, from minimal (mainly for assistance tasks to the preserved limb) to discrete (characterized by coarse manipulation and an inability to perform precision grip).c) Sufficient cooperation and cognitive understanding to participate to the activities, controlled by the investigator recruiting the patient.

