#### *Experimental treatment (AO* + *VR)*

Participants of the experimental group will undergo a treatment based on observation of actions followed by their immediate reproduction in VR (AO + VR treatment). The experimental treatment will consist in 18 sessions lasting about 1 h each, with a tolerance of ± 2 sessions, thus resulting in a minimum of 16 and a maximum of 20 sessions. Treatment sessions will be carried out with a frequency of about four days per week, within a period of five weeks. During the rehabilitation sessions, the patient will be instructed to carefully watch videos lasting about 1.5 min, presented on the monitor, consisting in unimanual or bimanual actions performed by an actor, from a lateral perspective (see Fig. 2-B1). Subsequently, the patient will be asked to imitate the actions presented for at least three consecutive times, within a time window of 3 min., using the same objects observed in the video, in a virtual scenario (VR), through the Khymeia VRRS system. During the execution of all exercises, the patient will wear also kinematic sensors for three-dimensional tracking of the performed movement, aimed to control objects in the virtual scenario. The treatment will include a total of 52 exercises, arranged as simple movements and complex sequences, either unimanual or bimanual, of increasing complexity. Examples of the proposed exercises are reported in Additional file 2. The protocol will include, for each week of training, a set of exercises subdivided in two parts, the first to be performed for two days, and the remaining to be performed in the remaining two days. For each exercise, the therapist will set the facilitation level, adjusting the sensitivity of kinematic sensors (levels range from 1 to 10) according to the patient's manual impairment. Facilitation level will be used particularly for those patients showing minimal residual hand ability, allowing them to perform the VR exercises. In more details, the exercises during the first week will include “no-gravity” movements (with no hand lifting) such as sliding to reach for a target located in different positions. The second and the third weeks will consists of “simple” and “complex” anti-gravity actions (requiring arm/hand lifting) respectively, either unimanual or bimanual. Furthermore, some bimanual functional exercises will be introduced, such as to put the toothbrushes in a glass, or to use knife and fork. The fourth week will consist of complex bimanual daily life actions, such as, for example, to wear sunglasses, or to draw a line with the ruler. Finally, during the fifth week, a set of more complex anti-gravity exercises will be proposed, including tasks of obstacles avoiding or following a path using a graspable floating pad device. Each session of AO + VR rehabilitation will take 30–45 min. to complete, including changing the setting between different exercises. The administration of personalized set of exercises will be adapted based on the patient hand motor performance at baseline, thus patients with minimal hand and arm ability will perform only no-gravity movements and simple anti-gravity actions, while patients with discrete hand ability will also perform the advanced exercises. Despite this type of adjustment of the treatment all the recruited patients will receive an equal number of treatment sessions, thus the final dose of the treatment will be balanced between the experimental and the control group.

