### Outcomes

#### Primary outcome

The primary outcome measure will be the Box and Block Test (BBT) [31, 32], a timed test for assessing upper limb dexterity and motor coordination. The test consists of 150 small wooden cubes (25 mm side) contained in a wooden box. The assessment will be performed by an investigator blinded to the assignment of the patient to the experimental or control group, before treatment (T0), after the conclusion of the treatment (T1, within 72 h of conclusion) and after 6 months, as a follow-up (T2).

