#### Secondary outcomes

The secondary outcome measures will include improvement in motor function indices and quality of life measures, i.e., modified Ashworth scale (MAS) [33, 34], Motricity Index [35], Rankin Scale (RS) [36], modified Barthel Index (mBI) [37]. These tests will be administered at both T0 and T1. A further assessment will be performed 6 months (T2) after the end of the treatment to evaluate the retention of the effect.

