#### Sample size

According to CONSORT guidelines [38, 39], the estimated sample size is based on projected treatment effects on the primary outcome measure, the BBT. Based on the available literature [32], we consider a 7-point change in BBT scores at post-test (T1) as a clinically significant effect. Based on a common standard deviation at post-test equal at 11.3 and a drop-out rate of 10%, we estimate that a sample of 47 subjects for each group (*N* = 94) will have a statistical power of 80% to detect a significant difference between the two measurements.

Concerning the fMRI study, the sample size estimate is based on the calculation of the level of change in the Blood Oxygenation Level Dependent (BOLD) signal detected in a previous fMRI study with an action observation paradigm (number of subjects per group = 10). Significant activation clusters within the MNS, including the PMv and the IPL, were considered for the analysis, using a statistical threshold of *p* < 0.001 with Family Wise Error (FWE) correction for multiple comparisons at the cluster level. The Power Analysis (software: NeuroPower-tool) conducted on this study showed that to obtain a change in the BOLD signal with a significance threshold of *p* < 0.05 and a minimum statistical power of 80% with Bonferroni correction, it is necessary to recruit at least 9 participants per group. However, regardless of the presence or absence of effects at the group level, patients will also be treated as a case-series, so that assessment of BOLD change following treatment will also be performed at the single case level.

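### The Box and Block Test may have a floor in the minimal-use stratum, yet the sample size assumes one 7-point effect and one SD for both randomised strata and the stated primary test ignores the stratum

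*Protocol article*

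**What the plan says.** **Who is enrolled.** The protocol article, Inclusion criteria, item b, describes active use of the paretic limb "from minimal (mainly for assistance tasks to the preserved limb) to discrete". The discrete level is itself "characterized by coarse manipulation and an inability to perform precision grip". Strength is "controlled by Medical Research Council (MRC) index (> 2 and < 4"). The Participants section excludes severe motor symptoms without giving a threshold. No minimum BBT score appears in the text. Under Randomization, minimal and discrete hand use are the two strata, with no cap or expected share for either.

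**What is measured.** Under Primary outcome, the BBT is "a timed test for assessing upper limb dexterity and motor coordination". On the materials used, that section adds: "The test consists of 150 small wooden cubes (25 mm side) contained in a wooden box".

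**What is trained.** Under Experimental treatment (AO + VR), "patients with minimal hand and arm ability will perform only no-gravity movements and simple anti-gravity actions", while discrete patients also do the advanced exercises. Sensor facilitation is meant mainly for patients with minimal residual hand ability. The control arm performs the same type of exercises.

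**What is assumed and tested.** Under Sample size, "we consider a 7-point change in BBT scores at post-test (T1) as a clinically significant effect", with a common SD of 11.3, 10% drop-out and 47 per group for 80% power. Under Statistical analyses, the primary endpoint is tested with an independent-samples t test (Mann-Whitney if normality fails), followed by a 2 × 3 repeated-measures ANOVA on group and time. Hand-use level is in neither.

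**The concern.** Eligibility, training content and primary outcome do not fit together well at the lower end. A patient who uses the arm mainly to help the other one, and who trains only on the simpler tasks, may move no blocks at T0 and none at T1, even if reach or strength improves. Such a patient adds nothing to the between-arm BBT difference, whichever treatment is given.

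Two planning choices make this matter. The sample size treats the 7-point effect and the SD of 11.3 as common to both strata, so any share of patients at the floor takes power below the stated 80%. The stated primary analysis also omits the factor that best separates likely floor patients from the rest, although it has already been used to stratify randomisation. A null pooled result would then be hard to interpret: the treatment might not work, or the outcome might not have been able to move in part of the sample.

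**Working it through.** **Inputs.** From Sample size: difference 7, SD 11.3, power 80%, drop-out 10%, 47 per group. From Statistical analyses: two-sided 5%, independent-samples t test. Assumed, because the documents give no BBT distribution: the share f of patients who score zero at T1 in both arms.

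**Step 1: reproduce the plan's figure.** Standardised difference = 7 / 11.3 = 0.619. The exact two-sample t calculation needs 41.9, so 42 evaluable per arm. 42 / 0.9 = 46.7, so 47 per group. This matches the protocol. Power with 42 per arm is 80.1%. The arithmetic is right; the question is the single-effect assumption.

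**Step 2: dilute the effect.** If a share f stays at zero in both arms and all others gain the planned 7 points, the pooled difference is 7 × (1 − f). The noncentrality is 7(1 − f) / 11.3 × √(42/2), and power comes from the noncentral t distribution on 82 degrees of freedom.

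| f (assumed) | Pooled difference | Noncentrality | Power, 42 per arm | Per group for 80%, with 10% drop-out |
|---|---|---|---|---|
| 0% | 7.0 | 2.84 | 80% | 47 |
| 10% | 6.3 | 2.55 | 71% | 58 |
| 20% | 5.6 | 2.27 | 61% | 73 |
| 30% | 4.9 | 1.99 | 50% | 95 |
| 50% | 3.5 | 1.42 | 29% | 184 |

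**Step 3: vary the SD.** Holding the SD at 11.3 is a second assumption, and it matters in both directions.
- If the pooled SD were 9 (assumed) at f = 20%, the standardised difference would be 5.6 / 9 = 0.622 and power about 80%.
- If 11.3 is instead the SD among non-floor patients, zeros widen the pooled spread. Simulation with assumed non-floor control means of 15 to 25 blocks gave power of 64% to 54% at f = 10%, 44% to 32% at 25%, and 22% to 15% at 50%.

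**Step 4: does using the stratum help?** Take equal strata (assumed), so 21 per arm in each, with the minimal stratum wholly at the floor (f = 50%). The discrete stratum alone has noncentrality 0.619 × √(21/2) = 2.01 on 40 degrees of freedom, which gives about 50% power. The pooled unstratified test has 29% (step 2). For smaller floor shares, simulation with equal strata and floor patients confined to the minimal stratum showed more power with the stratum in the model than without it at every non-zero share tried. The gain was slight when few patients were at the floor and grew with the share.

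**The case against.** The strongest reply is that no floor is shown. The inclusion text says the limb is used mainly, not only, for assistance. Entry also requires active use and more than MRC grade 2, and severe motor symptoms are excluded. Minimal-use patients still train simple anti-gravity actions, which involve lifting the arm or hand. A score of zero at T0 leaves full room to rise. All of this stands, and it rules out the stronger reading that the BBT cannot show benefit in this stratum: benefit is hidden only in patients who remain at zero at T1. It does not remove the risk, because MRC grades strength rather than the ability to grasp and release a block.

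A reader might also infer that discrete patients are at the floor because they lack precision grip. The article does not say that the BBT needs precision grip, and it credits these patients with coarse manipulation. Nor do the remarks in the Background and Discussion on severe impairment carry over directly. They concern conditions where intensive training is not feasible, whereas everyone enrolled here is to receive 16 to 20 sessions.

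Stratum estimates may be planned in an analysis plan that is not shown, so their absence from the article is not in itself the point. The point is that the article fixes a primary test and a group-by-time model without the stratum, and a sample size with one effect for all. The secondary outcomes, including "modified Ashworth scale (MAS) [33, 34], Motricity Index [35"], would pick up some gains that the BBT misses, so a null BBT result would not be the only evidence.

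Finally, stratum estimates do not restore the planned power. That is true, but step 4 shows that using the stratum recovers part of the loss if a floor exists.

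**Conclusion.** The point holds as a risk. The BBT may have a floor effect in the minimal-use stratum, and neither the sample size nor the stated primary analysis allows for it. If 10% to 50% of patients stay at zero in both arms, power falls from 80% to between about 71% and 29%. This rests on three assumptions: the floor share, which the documents do not give; an SD held at 11.3; and a full 7-point gain in everyone else. Step 3 shows that the figures move materially with the SD, so they are a range and not an estimate.

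A reader might infer a biased comparison. The documents do not support that: 1:1 randomisation stratified by hand use should balance likely floor patients between arms, so the expected harm is dilution and lost power. The Mann-Whitney fallback addresses non-normality but removes neither the dilution nor the ties at zero. Fig. 1 was not available for this review and lists the BBT among its abbreviations, so an entry rule there cannot be excluded.

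**What to change.** Leave enrolment as it is and change the analysis wording:

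1. Include the randomised hand-use stratum in the primary BBT analysis.
2. Prespecify the AO + VR minus CO + VR estimate with its confidence interval within each stratum, beside the pooled one.
3. Report the number scoring zero on the BBT at T0 and at T1, by arm and stratum.
4. State under Sample size that the 80% power assumes the 7-point effect holds in both strata.

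The article reports that recruitment had not started, so all of this can be prespecified, and it needs no data beyond those already planned. The cost is that stratum estimates are imprecise: with equal strata (assumed, 21 evaluable per arm in each), power is about 50% in each for the planned effect. They should be read as supportive.

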### Exclusion criteria

a) Presence of severe cognitive impairment (score < 20 at Mini Mental State Examination [MMSE]).b) Presence of severe forms of unilateral spatial neglect, controlled using the Bells Test (cut-off = / > 50%) [29].c) Presence of severe ideomotor Apraxia [30].d) Presence of severe anosognosia, assessed by clinical examination.e) Presence of severe language comprehension deficits, assessed by clinical examination.f) Presence of severe untreated psychiatric disorders.g) Sensory impairments hindering participation and/or not compensated visual deficits of central origin.h) Drug-resistant epilepsy.

A subgroup of patients will be selected to perform a magnetic resonance imaging (MRI) assessment. For these participants (approximately 10 for each group), additional exclusion criteria will be:a) Insufficient cooperation to perform neuroimaging studies lasting approximately 45 min.b) Presence of exclusions for 3 T MRI investigations (such as metal implants, prostheses, shunts, etc.). These exclusions will be controlled using an ad hoc questionnaire.

### Interventions

#### Setting for VR rehabilitation

Each rehabilitation session will take place in a quiet room, with the patient sitting on a chair with the arms placed on a table. To provide a suitable range of movement of upper limbs, the patient’s chair will be adjusted so that the table will be at waist height (Fig. 2-A). A large monitor screen (32 inches) will be positioned 1.5 m distance in front of the patient. A trained occupational therapist (OT) or a physiotherapist (PT) will assist the participants, instructing them to pay attention to the video-clips and encouraging them during the imitation task. The Virtual Reality Rehabilitation System (VRRS, Khymeia Group, Noventa Padovana, Italy) will be used for the execution of all exercises in a VR setting. The VRRS is used as a clinical routine for the rehabilitation of a wide spectrum of diseases through the numerous rehabilitation modules containing a large library of clinically validated exercises. The system includes also a workstation connected to a 3D motion tracking system (Polhemus Liberty TM, Colchester, VT) and an integrated high-resolution monitor for the visualization of virtual scenarios.

**Fig. 2 Fig2:**
[figure not shown]
(**A**) Experimental setting for both AO + VR and CO + VR interventions. (**B1**) Static frame showing an example of video-clip to be used for the experimental treatment AO + VR based on observation of actions performed by a model followed by subsequent imitation. (**B2**) Static frame of a video-clip illustrating natural scene, to be used in the CO + VR control treatment

#### *Experimental treatment (AO* + *VR)*

Participants of the experimental group will undergo a treatment based on observation of actions followed by their immediate reproduction in VR (AO + VR treatment). The experimental treatment will consist in 18 sessions lasting about 1 h each, with a tolerance of ± 2 sessions, thus resulting in a minimum of 16 and a maximum of 20 sessions. Treatment sessions will be carried out with a frequency of about four days per week, within a period of five weeks. During the rehabilitation sessions, the patient will be instructed to carefully watch videos lasting about 1.5 min, presented on the monitor, consisting in unimanual or bimanual actions performed by an actor, from a lateral perspective (see Fig. 2-B1). Subsequently, the patient will be asked to imitate the actions presented for at least three consecutive times, within a time window of 3 min., using the same objects observed in the video, in a virtual scenario (VR), through the Khymeia VRRS system. During the execution of all exercises, the patient will wear also kinematic sensors for three-dimensional tracking of the performed movement, aimed to control objects in the virtual scenario. The treatment will include a total of 52 exercises, arranged as simple movements and complex sequences, either unimanual or bimanual, of increasing complexity. Examples of the proposed exercises are reported in Additional file 2. The protocol will include, for each week of training, a set of exercises subdivided in two parts, the first to be performed for two days, and the remaining to be performed in the remaining two days. For each exercise, the therapist will set the facilitation level, adjusting the sensitivity of kinematic sensors (levels range from 1 to 10) according to the patient's manual impairment. Facilitation level will be used particularly for those patients showing minimal residual hand ability, allowing them to perform the VR exercises. In more details, the exercises during the first week will include “no-gravity” movements (with no hand lifting) such as sliding to reach for a target located in different positions. The second and the third weeks will consists of “simple” and “complex” anti-gravity actions (requiring arm/hand lifting) respectively, either unimanual or bimanual. Furthermore, some bimanual functional exercises will be introduced, such as to put the toothbrushes in a glass, or to use knife and fork. The fourth week will consist of complex bimanual daily life actions, such as, for example, to wear sunglasses, or to draw a line with the ruler. Finally, during the fifth week, a set of more complex anti-gravity exercises will be proposed, including tasks of obstacles avoiding or following a path using a graspable floating pad device. Each session of AO + VR rehabilitation will take 30–45 min. to complete, including changing the setting between different exercises. The administration of personalized set of exercises will be adapted based on the patient hand motor performance at baseline, thus patients with minimal hand and arm ability will perform only no-gravity movements and simple anti-gravity actions, while patients with discrete hand ability will also perform the advanced exercises. Despite this type of adjustment of the treatment all the recruited patients will receive an equal number of treatment sessions, thus the final dose of the treatment will be balanced between the experimental and the control group.

#### *Control treatment (CO* + *VR)*

Participants randomly assigned to the control group will receive an equal number of rehabilitation sessions, as the experimental group. Differently from the latter, patients of the control group will be required to observe videos depicting naturalistic scenes (Fig. 2-B2), without motor contents, for 1.5 min. Then, they will receive a motor training in the VR environment, performing the same type of exercises included in the above-described experimental treatment, prompted by the verbal instructions of an expert therapist. Thus, the general setting for carrying out the rehabilitation sessions will be identical to that of the experimental group, except for the fact that the control group will not be involved in action observation before preforming the exercises. Thus, the control treatment is not based on action imitation, but on purely motor execution.

### Modifications

Temporary suspension of the treatment will be recommended if participants will not be able to perform the VR exercises. The trial will then restart as soon as the patient will be able to participate in the activities. The final decision on the possibility to terminate the trial will belong to the principal investigator. Any adverse event will also be reported using a specific form.

### Adherence reminder sessions

Face-to-face adherence reminder sessions will take place at the beginning of the treatment and after the conclusion of its first part. During these sessions, a member of the staff will provide participants with all instructions about the treatment procedures. In addition, these sessions will be used to reinforce the adherence to the rehabilitation sessions.

### Concomitant care

Participants will continue to take medications for other conditions and rehabilitation treatments as usual care.

#### Monitor committee

Monitoring activity will be guaranteed by the Clinical Trial Quality Team (CTQT) of the University Hospital of Parma (Parma, Italy).

### Outcomes

#### Primary outcome

The primary outcome measure will be the Box and Block Test (BBT) [31, 32], a timed test for assessing upper limb dexterity and motor coordination. The test consists of 150 small wooden cubes (25 mm side) contained in a wooden box. The assessment will be performed by an investigator blinded to the assignment of the patient to the experimental or control group, before treatment (T0), after the conclusion of the treatment (T1, within 72 h of conclusion) and after 6 months, as a follow-up (T2).

